## Abstract

**Background:**

Neuropathic pain is a common pain condition that has a major negative impact on health-related quality of life. However, despite decades of research, it remains difficult to treat neuropathic pain. Lacosamide is a sodium-channel blocker that is efficacious in animal models of neuropathic pain. In humans, its effect in neuropathic pain is inconclusive, based on inconsistent results and very large placebo responses. Previous trials have not used patient stratification or looked for predictors for response.

**Methods:**

This study will be conducted as a multicenter, randomized, double-blind, placebo-controlled, parallel, phase 2, proof-of-concept, phenotype-stratified study. The study will enroll 108 patients with peripheral neuropathic pain who will be randomized to a 12-week treatment with lacosamide or placebo up to 400 mg/day in a 2:1 ratio. The primary objective is to compare the change in the mean value of the patients’ daily ratings of average pain intensity from baseline to the last week of treatment in patients with and without the irritable nociceptor phenotype in the per-protocol population. A supportive objective is to compare the effect of lacosamide with that of placebo in the two phenotypes. Secondary and tertiary outcomes include the Patient Global Impression of Change, pain relief, presence of 30% and 50% pain reduction, sleep disturbance, depression, and anxiety.

**Discussion:**

We will examine the concept of individualized therapy based on phenotyping, and expect that this study will provide important information on the usefulness of lacosamide in the treatment of peripheral neuropathic pain.

**Trial registration:**

ClinicalTrials.gov, NCT03777956. Registered on 18 December 2018.

**Electronic supplementary material:**

The online version of this article (10.1186/s13063-019-3695-7) contains supplementary material, which is available to authorized users.

## Background

Neuropathic pain is a common pain condition that has a major negative impact on health-related quality of life [1]. Despite many years of intensive research into the prevention and management of this pain condition, it remains difficult to treat. Evidence-based recommendations list three drug classes as first-line therapies: tricyclic antidepressants (TCAs), α2δ calcium channel ligands (gabapentin and pregabalin), and serotonin and noradrenaline re-uptake inhibitors (SNRIs) (duloxetine, and venlafaxine) [2]. However, many patients are left with no or limited pain relief using these drugs in maximum tolerated doses or drug combinations. There is therefore an urgent need for other drugs for treating neuropathic pain. There is increasing interest in identifying predictive biomarkers associated with a specific tractable pain mechanism linked to a drug with a known mechanism of action [3, 4]. One promising approach is to use quantitative sensory testing (QST), which involves standardized mechanical and thermal stimuli to assess loss (negative signs) and gain (positive signs) of sensory function. In a phenotype-stratified randomized, double-blind, placebo-controlled study, our research group has recently shown that the sodium channel blocker oxcarbazepine reduced pain more in patients with the so-called irritable nociceptor phenotype than in patients without this phenotype [5]. In addition, a malfunctioning descending pain modulation (e.g. assessed by the conditioned pain modulation (CPM) test) [6] and patient-reported outcomes assessed with validated questionnaires such as the Neuropathic Pain Symptom Inventory (NPSI) may represent predictive biomarkers for drug efficacy [7].

Lacosamide is a functionalized amino acid molecule, developed as an antiepileptic drug. It selectively enhances the slow inactivation of voltage-gated sodium channels and interacts with the collapsin-response mediator protein-2 (CRMP-2), which is involved in neurotrophic pathways [8]. Lacosamide is efficacious in animal models of neuropathic pain [9]. In humans, the effect of lacosamide on neuropathic pain is inconclusive, based on inconsistent results and very large placebo responses (i.e. a large reduction in pain intensity during placebo treatment) in the few randomized controlled trials (RCTs) [2, 10–13]. Improvements were seen for secondary variables such as sleep, patient global impression of change (PGIC), quality of life, and pain interference; and two trials with multiple dosing showed efficacy of lacosamide 400 mg on the primary outcome [11, 12]. Recently, a study in patients with SCNA9A-associated painful small-fiber polyneuropathy has been carried out [14]. These studies did not reveal serious or clinically relevant safety issues, and the majority of reported adverse events (most commonly dizziness, nausea, and headache) were mild to moderate. Previous lacosamide trials have not used patient stratification or looked for predictors. The aim of this study is therefore to assess whether specific pain phenotypes based on sensory testing are linked to an increased response to lacosamide in patients with peripheral neuropathic pain.

Standard Protocol Items: Recommendations for Interventional Trials (SPIRIT) were used in writing this manuscript (see Fig. 1 and Additional file 1).

**Fig. 1 Fig1:**
[figure not shown]
Standard Protocol Items: Recommendations for Interventional Trials (SPIRIT) figure. Schedule of enrolment, interventions, and assessment. ^1^The 3-week follow-up includes a 1-week tapering down and a 2-week follow-up with no medication. Telephone call after the 3-week follow-up. In the case of unresolved side effects at this call, an additional call is scheduled after 1–4 weeks. ^2^Patients treated with pregabalin will come for an extra visit. ECG electrocardiogram, PGIC Patient Global Impression of Change

## Methods/design

### Objective

The primary objective is to compare the change in average intensity of neuropathic pain from the baseline week to the last week of lacosamide treatment in patients with and without the irritable nociceptor phenotype who complete at least 2 weeks on stable medication with at least 100 mg bid; that is, in the per-protocol (PP) population (Fig. 2).

**Fig. 2 Fig2:**
[figure not shown]
Primary and supportive objectives. IN irritable nociceptor, NIN non-irritable nociceptor, R randomization

The supportive objective is to compare the effect of lacosamide with placebo in the two phenotype groups in the PP population (Fig. 2). Although we do not expect a phenotype difference in the response to placebo, a comparison of the effect of lacosamide versus placebo is needed to justify that the phenotype is a predictive biomarker for the effect of lacosamide.

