### Statistics

With a minimally relevant between-phenotype group difference in total pain reduction of 1.25 NRS points, a standard deviation of 1.6 within phenotype groups [5], 80% power, and a 5% risk of type I error, the sample size estimate is 27 + 27 patients for the primary objective. With a minimally relevant treatment versus placebo difference in total pain reduction of 1.5 NRS points, 80% power, and a 5% risk of type I error, the sample size estimate is 30 + 15 patients using a treatment:placebo ratio of 2:1 for the supportive objective. With an expected dropout rate of 1/6 (data available for intention-to-treat (ITT) analysis), the recruitment stops when 54 patients in each phenotype group have been randomized to lacosamide and placebo in a 2:1 ratio. Thus, we expect to randomize 108 patients. For the explorative outcome in case there is no phenotype difference, 72 patients randomized to lacosamide and 36 patients randomized to placebo in the total population in an ITT population will give > 90% power to find a minimally relevant treatment versus placebo difference in total pain reduction of 1.25 NRS points and 85% power to find a minimally relevant treatment versus placebo difference in total pain reduction of 1.0 NRS points.

Statistical analysis of the primary outcome will be performed by *t* test and of the secondary outcomes by the Mann–Whitney *U* test. Nondichotomous tertiary outcomes will be performed by *t* test or Mann–Whitney *U* test, where applicable. Since we do not expect differences in baseline between the two phenotypes [5], a major impact of baseline pain intensity on the outcome, or a center effect, we do not plan to include these as covariates in the analyses.

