For the primary outcome, the delta values from the average pain intensity in the baseline week to the last treatment week (last 7 days) will be used. Response rates and other dichotomous data are analyzed using Fisher’s exact test. For the primary (and supportive) objective, we are interested in the mechanistic aspects and in understanding whether the sensory phenotype “irritable nociceptor” is a prognostic biomarker for a sodium channel blocker in therapeutic doses. Therefore, the primary analysis for the primary objective is the PP population. Missing data will not be replaced. The PP population comprises those patients who complete at least 2 weeks on stable medication with at least 100 mg bid. Thus, if patients who fulfil the PP definition stop the treatment before the 12th week, the last seven pain scores on stable medication will be used for the primary analysis, and they will be invited for an additional visit identical to visit 3. All patients who have taken at least one study capsule will be encouraged to stay in the study, complete the diary, and come for a visit after 12 weeks.

As a secondary analysis, the ITT population will be used. The ITT analysis will also be used for the explorative outcome in the whole population if there is no phenotype difference. Given a substantial dose-dependent withdrawal rate due to adverse events, the EMA suggests a conservative responder analysis and that noncompleters are defined as nonresponders [19]. Therefore, the baseline observation carried forward (BOCF) in the ITT population (all patients randomized) will be the primary imputation method, and the last observation carried forward (LOCF) will be done as a secondary imputation method. Patients will be asked to complete the pain diaries despite their withdrawal from trial medication to minimize the need for imputation.

Significance is considered at the 5% level. If there are changes to the original statistical plan, the type of change and the date of change will be documented, and the document will be signed by the sponsor.

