## Discussion

The main aim of this study is to assess the concept of stratification based on pain phenotyping in neuropathic pain. We aim to assess whether we can reproduce results from a previous study showing a better effect of the sodium channel blocker oxarbazepine in patients with neuropathic pain and the so-called irritable nociceptor phenotype [5]. Lacosamide is a sodium channel blocker with a different profile enhancing the slow-inactivation of voltage-dependent sodium channels [8]. The strength of the study is that the primary purpose is to compare the effect in two groups of patients with different sensory pain phenotypes and thus possible different underlying pain mechanisms and blinding of persons involved in the study to the pain phenotype. There are several limitations. An unrealistically high number of patients would be required to power the study to show a difference in the drug–placebo differential between the two groups of patients, so the study will need to rely on supportive evidence. A thorough analysis of previous studies would have been advantageous to assess whether the best statistical plan should be a regression analysis including, for example, baseline pain intensity, center, and escape medication. There is a possibility of discontinuation due to lacosamide’s potential side effects and a risk of unblinding due to side effects. In addition, we do not know the strength and reproducibility of the phenotype classification as only one sensory testing will be performed, and the classification into IN and NIN can be considered an arbitrary dichotomy of continuous measurements [20].

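### The contrasts said to justify a predictive biomarker never estimate the phenotype difference in drug–placebo effect, leaving a prognostic gap combined with an active drug unguarded

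*Protocol article*

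**What the plan says.** The Objective section defines the primary contrast as the change in pain "from the baseline week to the last week of lacosamide treatment in patients with and without the irritable nociceptor phenotype", in the per-protocol (PP) population. The text after Fig. 2 adds: "The supportive objective is to compare the effect of lacosamide with placebo in the two phenotype groups in the PP population". On equal placebo response it offers an expectation only ("Although we do not expect a phenotype difference in the response to placebo"). It then gives the reason for making the supportive comparison all the same: "a comparison of the effect of lacosamide versus placebo is needed to justify that the phenotype is a predictive biomarker".

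The Statistics section sizes the primary contrast at 27 + 27 and the supportive one at 30 + 15. It plans a *t* test for the primary outcome and no baseline or centre covariates. No phenotype-by-treatment contrast is stated. The same section describes the question as whether the phenotype "is a prognostic biomarker for a sodium channel blocker in therapeutic doses", which is a different property from the one named under Objective.

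The Discussion concedes that powering the between-phenotype difference in drug–placebo effect would take an unrealistic number of patients, "so the study will need to rely on supportive evidence".

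**The concern.** A prognostic marker goes with a better course whatever the treatment. A predictive marker goes with a larger effect of the drug over placebo. Phenotype is not randomised, so the lacosamide-only comparison contains any phenotype difference in placebo response, natural course or regression to the mean, as well as any difference in drug effect. The drug–placebo comparisons within phenotype are randomised, but a significant result in one and a non-significant result in the other is not a test that the two effects differ.

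At stake is the trial's central conclusion. If IN patients improve somewhat more on any treatment and lacosamide works equally in both phenotypes, the planned results can look like a predictive biomarker when there is none.

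**Working it through.** **Inputs.** From Statistics: "With a minimally relevant between-phenotype group difference in total pain reduction of 1.25 NRS points"; "a standard deviation of 1.6 within phenotype groups"; 1.5 points for drug versus placebo; 2:1 allocation; 80% power; 5% level; dropout 1/6; 54 randomised per phenotype. Assumed: two-sided tests, and SD 1.6 for the supportive objective too (both reproduce the stated sizes), with 30 + 15 analysable per phenotype.

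**The plan's own figures reproduce.**
- Primary, noncentral *t*: 27 + 27 gives 80.4% power for 1.25 points.
- Supportive: 30 + 15 gives 82.6% for 1.5 points.
- Dropout: 45 / (1 − 1/6) = 54 per phenotype, 108 in total.

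There is no arithmetic error. The issue is what the contrasts estimate.

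**What each contrast estimates.** Let *g* be the prognostic gap (extra improvement in IN on any treatment), *d* the drug effect in NIN, *i* the extra drug effect in IN, and μ the mean improvement of NIN on placebo.

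| | Lacosamide | Placebo |
|---|---|---|
| IN | μ + g + d + i | μ + g |
| NIN | μ + d | μ |

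- Primary (IN − NIN on lacosamide): *g + i*
- Supportive within IN: *d + i*; within NIN: *d*
- Four-cell contrast (IN drug–placebo minus NIN drug–placebo): *i*

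Only the last isolates *i*, the predictive quantity. It can be formed by subtracting the two supportive estimates, but the article does not state that step or an interval for it.

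**Joint behaviour when *i* = 0.** I simulated 200,000 trials per row with normal outcomes. The IN-only pattern means the primary test favours IN, drug–placebo is significant in IN, and it is not significant in NIN.

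| Gap *g* | Drug effect *d* | Primary and IN test both positive | IN-only pattern |
|---|---|---|---|
| 0.5 | 0 | 1.5% | 1.5% |
| 0.75 | 0 | 2% | 2% |
| 1.25 | 0 | 2% | 2% |
| 0 | 1.0 | 2% | 2% |
| 0.5 | 1.0 | 16% | 11% |
| 0.75 | 1.0 | 28% | 17% |
| 1.25 | 1.0 | 45% | 24% |

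At a gap of 1.25, changing the equal drug effect to 0.75 or 1.5 points gives the IN-only pattern in about 21% or 14% of trials. A test of the four-cell contrast stays at 5% in all these cases.

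**Precision of the four-cell contrast at the planned size.**
- SE = 1.6 × √(2/30 + 2/15) = 1.6 × √0.2 = 0.716
- df = 90 − 4 = 86, so the 95% half-width = 1.988 × 0.716 = 1.42 points
- Power: 41% for a true 1.25-point difference and 79% for 2.0 points
- 80% power for 1.25 points needs 78 + 39 per phenotype, or 234 analysable. Allowing for dropout, 117 / (5/6) = 140.4, so 141 per phenotype and 282 randomised, against 108 planned.

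**The case against.** The authors disclose that the differential is not powered, and 282 against 108 bears them out. This is a phase 2 proof-of-concept study. The drug–placebo comparison is presented as an addition to the primary contrast, so the two must be judged together, and together they err in only about 2% of trials when just one of the two problems is present. The size of any prognostic gap is my assumption; the authors expect none on placebo. All of this stands. It explains why the trial is not sized on the interaction. It does not make the stated comparison sufficient for a predictive claim.

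A reader might infer more than the documents support:

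- *That the plan cannot tell a predictive from a prognostic marker at all.* This is too strong, because the supportive comparison largely screens out a prognostic phenotype with an inactive drug.
- *That the false-claim rate is 22% or 43%* (primary test alone, gap 0.5 or 0.75) *or 25%* (IN-only on the two supportive tests alone, equal 1.0-point effect). These score one component at a time, whereas the article requires both.
- *That the article sets a rule of significant in IN, not in NIN.* It states no such decision rule; the pattern is used here to gauge how results might be read.
- *That equal placebo response will be tested between phenotypes.* Only an expectation is stated. The exploratory objectives relate change on both treatments to QST components and look at placebo-response predictors, but state no phenotype-by-treatment contrast.
- *That the authors have refused to report the interaction.* They say only that it is not powered, and a separate analysis plan might add it. The point rests on the inference the article itself draws from its stated contrasts.
- *That the analysis must move to all randomised patients with baseline adjustment.* The article gives reasons for the PP population and for omitting covariates, and this defect does not require changing either.

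**Conclusion.** The point holds in a bounded form. The article ties its predictive justification to comparisons that do not estimate the difference in drug–placebo effect between phenotypes. The exposure is specific: a prognostic gap together with a drug active in both phenotypes. Under SD 1.6, 30 + 15 analysable per phenotype and an equal 1.0-point effect, gaps of 0.5 to 1.25 points produce the misleading pattern in about 11% to 24% of trials. The documents give no figure for the gap, so these are a range under assumption and not a forecast. If fewer than 30 + 15 per phenotype meet the PP definition, the interval for the interaction widens further.

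Separately, the Objective and Statistics sections use terms with different meanings for the same target. The Objective text makes the intended meaning clear.

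**What to change.** 1. Keep the lacosamide-only IN versus NIN contrast as the powered primary test.
2. Prespecify, before unblinding, the four-cell contrast (IN drug–placebo difference minus NIN drug–placebo difference) with its 95% CI as the key supportive estimate. Use the PP population, with ITT as the secondary analysis. It needs no covariates.
3. State that it is reported as an estimate and not as a powered test. Requiring significance would miss a true 1.25-point difference 59% of the time (1 − 0.41).
4. Word the conclusion by that estimate and its interval. Where they do not support a difference, report a phenotype difference under lacosamide that has not been shown to be drug-specific.
5. Change prognostic to predictive in the Statistics section so that it agrees with Objective.

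The cost is some wording and one linear contrast of four means, with no extra patients. The downside is a less favourable claim when the interval is wide, which at a half-width of about 1.4 points is likely.

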### Exploratory objectives

To analyze whether the change in pain intensity from baseline to the last week of lacosamide and placebo treatment depends on preserved thermal sensation (QST), gain of sensation (QST), pain characteristics as determined by the NPSI, or evoked pain ratings in the bedside sensory testingIf there is no phenotype difference, we will compare the primary and secondary outcomes in the total populationTo analyze whether there is a correlation between the percentage change in pain score from the baseline week to the last week of treatment and the effect of conditioned pain modulation (CPM) [6]To analyze predictors of the placebo response (CPM, patient expectation, age, gender, anxiety and depression scores at first examination, pain duration, baseline pain variability, and adverse events)

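### The exploratory CPM objective has no lacosamide–placebo contrast, so no stated analysis tests whether CPM modifies the lacosamide effect

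*Protocol article*

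**What the plan says.** All references are to the Protocol article.

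- **Exploratory objectives, CPM item:** the analysis is "a correlation between the percentage change in pain score from the baseline week to the last week of treatment", with CPM as the other variable. This fixes a method (correlation) and a scale (percentage change). It names neither an arm nor a treatment contrast.
- **Exploratory objectives, last item:** "To analyze predictors of the placebo response (CPM, patient expectation" and further patient characteristics. CPM against placebo response is therefore planned.
- **Exploratory objectives, first item:** this asks whether the change in pain to "the last week of lacosamide and placebo treatment depends on preserved thermal sensation (QST") and other sensory and symptom measures. Both arms are named, but CPM is not on its list.
- **Background:** a malfunctioning descending pain modulation, for example as measured by CPM, and questionnaire measures "may represent predictive biomarkers for drug efficacy".
- **Objective, supportive objective (text at Fig. 2):** "a comparison of the effect of lacosamide versus placebo is needed to justify that the phenotype is a predictive biomarker", meaning one that predicts response to lacosamide.
- **Statistics:** on the primary analysis variable, "the delta values from the average pain intensity in the baseline week to the last treatment week (last 7 days) will be used", so the primary scale is absolute change. On baseline pain intensity and center: "we do not plan to include these as covariates in the analyses".

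**The concern.** The reason given for measuring CPM is that it might predict drug efficacy. That is a question about effect modification: does the difference between lacosamide and placebo vary with CPM? A correlation of CPM with pain change does not address it. A patient with a given CPM result may improve more on either treatment, and the protocol itself lists CPM as a candidate predictor of placebo response. The article applies the right reasoning to the phenotype, where it calls for a placebo comparison, but states no such comparison for CPM.

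The scale is a lesser point. Percentage change divides by baseline pain, so if CPM is related to baseline pain, part of the correlation can come from the denominator.

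At stake is how an exploratory result is interpreted. A correlation driven by placebo response, by general response or by baseline pain could be taken as support for CPM as a lacosamide marker, and a real drug-specific association could be diluted and missed.

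**Working it through.** **Plan figures.** The article gives none for the CPM objective. The arm sizes come from Statistics and reproduce: 30 + 15 = 45 per phenotype, 45 / (5/6) = 54, and 2 × 54 = 108; at 2:1 this is 72 lacosamide and 36 placebo. Also from the article: baseline pain 4 to 9, SD of change 1.6, 5% significance level (taken as two-sided).

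**1. What pooling does.** Without baseline effects, the pooled CPM slope is the weighted mean of the arm slopes, (72 × lacosamide + 36 × placebo) / 108.

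- 0.30 in both arms: 0.30.
- 0.15 lacosamide, 0.60 placebo: (2 × 0.15 + 0.60) / 3 = 0.30.

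The drug effect adds variance between arms, which shrinks both. With SD 1.6 and an assumed drug effect of 1.25: 0.30 × 1.6 / √(1.6² + 1.25² × 2/9) = 0.30 × 1.6 / 1.705 = 0.28 on the absolute scale. Simulated on the percentage scale (assumed baseline mean 6.5, SD 1.3, restricted to 4–9; mean placebo reduction 1.0), both cases give 0.27. One pooled number cannot tell them apart.

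**2. Rejection rates at 72 + 36.** The simulation assumes baseline mean 6, SD 1.5, restricted to 4–9; mean change −1.2 on placebo and a further −1.0 on lacosamide; residual SD 1.55; follow-up limited to 0–10. Slopes are in residual SDs per SD of CPM.

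| True CPM slopes | Pooled percentage-change correlation | CPM × treatment, baseline-adjusted |
|---|---|---|
| Opposite signs, 0.3 each | 15% | 80% |
| Placebo arm only, 0.4 | 24–25% | 47–48% |
| Lacosamide arm only, 0.4 | 69% | 48% |
| Same sign, 0.3 in both | about 80% | 5% |

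In the last row CPM does not modify the drug effect, so 5% is the correct rejection rate for the interaction. In that same scenario a correlation in the lacosamide arm alone is significant in 65% of trials. Splitting by arm therefore does not turn the correlation into a test of effect modification.

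Hand check of the interaction: the standard error of the slope difference is about √(1/72 + 1/36) = 0.204. For a difference of 0.4, 0.4 / 0.204 = 1.96, so power is about 50%. For 0.6, 0.6 / 0.204 = 2.94, so power is about Φ(2.94 − 1.96) = 84%. The simulated values are slightly lower because follow-up is limited to 0–10.

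**3. Baseline pain.** A 1.5-point fall is 1.5 / 4 = 37.5% at baseline 4 and 1.5 / 9 = 16.7% at baseline 9. The rates below assume no CPM effect and a CPM–baseline correlation of 0.3 to 0.4.

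- Absolute change unrelated to baseline: the percentage-change correlation is falsely significant in about 9% to 13% of trials (repeat runs gave 8% to 14%, depending on whether the correlation is imposed before or after restricting baseline). The baseline-adjusted model stays at 5%.
- Change falls by 0.2 per baseline point: percentage change gives about 5–6%, and unadjusted absolute change gives about 7–9%.

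Which unadjusted scale carries baseline pain depends on how change relates to baseline. The adjusted model held about 5% in each of these null cases.

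**4. What by-arm correlations can detect.** With 80% power, the smallest detectable correlation is tanh(2.80 / √(n − 3)): 0.33 at n = 72, 0.45 at n = 36, and 0.27 for all 108.

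**The case against.** The article never says the arms will be pooled. A by-arm correlation fits the wording, and arm handling for one exploratory item could sit in the full protocol or analysis plan, which are not shown. The stated question is only whether a correlation exists, and a correlation answers that. Percentage change is not foreign to the trial, since the 30% and 50% responder outcomes use it. The documents give no CPM–baseline correlation and no basis for opposite slopes. The Discussion already says that powering a difference in the drug–placebo differential between the phenotype groups would need an unrealistic number of patients, and a CPM-by-treatment term is a similar contrast.

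Most of this stands, and it rules out stronger readings:

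- A reader might infer that the protocol pools the arms. It does not say so; pooling is one possible reading.
- A reader might infer that CPM and placebo response goes unexamined. The last exploratory objective covers it.
- A reader might infer that percentage change is an error, or that the result will be confounded by baseline pain. A different scale for an exploratory objective is not an error, the inflation depends on an unsupported assumption, and absolute change can carry baseline pain too.

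What the objection does not remove: the article commits to a correlation, and a correlation, pooled or by arm, does not compare lacosamide with placebo. Low power is a reason to report the interaction cautiously. It does not make the correlation an answer to the question that the Background raises.

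**Conclusion.** The point holds in a limited form. No analysis stated in the article tests whether CPM modifies the lacosamide effect, although the Background motivates that question and the article's reasoning about the phenotype shows what it would take. If the arms are pooled, drug and placebo response cannot be separated; if they are split, their difference is still not tested.

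The size depends on assumptions about CPM slopes that the documents do not supply. The gap between 15% and 80% needs slopes of opposite sign and is an extreme case. If CPM acts in the placebo arm only, the pooled correlation is significant in about a quarter of trials, which could be misread as drug prediction. The baseline-pain issue is secondary and conditional: about 9–13% false positives in one setting and about 6% in another.

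Severity is low. The objective is exploratory, and no sample size, primary or supportive analysis, or error rate rests on it.

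**What to change.** State the CPM analysis as a linear model of last-week mean pain on baseline-week mean pain, treatment, CPM effect (continuous) and CPM × treatment. Report the CPM slope in each arm and the difference between slopes, each with a 95% confidence interval. Keep the percentage-change correlation, shown by arm, as description. Label the result exploratory.

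The cost is a sentence or two in the analysis plan and no new data. The downside is precision. With 72 + 36 patients the 95% interval for the slope difference extends about 1.96 × 0.204 = 0.40 residual SD per SD of CPM either way, and power is about 47–48% if CPM acts in one arm only with a slope of 0.4. A non-significant interaction should therefore not be reported as evidence that CPM has no predictive value.
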